#### 4.5. List exclusion criteria

IFD or Fishers members not eligible for study consent and participation will include those:

a) without a recorded fire department exam in the last two years; b) less than 18 years of age.

#### 4.6. Describe study procedures

Human subjects-trained staff from Public Safety Medical (PSM) working with the IFD/ Fishers Chiefs and firefighters’ local union presidents will announce the inauguration of the study to IFD/ Fishers members and their opportunity to participate. Next, PSM staff will approach eligible IFD/ Fishers members for informed consent (see section 6.1).

##### Baseline Assessment:

- Using established coded data transfer methods between Public Safety Medical and the Harvard TH Chan School of Public Health. Public Safety Medical will transfer the results of the last existing fire department medical examination to the Harvard Chan research team for consented participants only.
- Medical exam data that will be provided to the study team for consented IFD/ Fishers subjects include: at rest and maximal heart rate, systolic and diastolic blood pressure, heart rate recovery, electrocardiographic findings at rest, hip and waist circumference, body composition, data regarding the grip strength, leg-press and push-ups performed, and routine lab values (e.g. lipid panels, hs-CRP and glucose).
- The medical exams will be supplemented by a comprehensive nutritional-lifestyle questionnaire (see attached). The survey instrument combines our existing mMDS with other validated scores and nutrition questionnaires. It also includes items on physical activity and other health behaviors to adjust for appropriate covariates. These questionnaires will be self-administered online via Qualtrics on a password-protected site. The comprehensive nutritional-lifestyle questionnaire should take between 20-45 minutes to complete.

In addition, the baseline assessment will include anthropometric measures (height, weight and body fat estimates (Tanita) and resting blood pressure will be taken in private areas of the fire houses by trained Public Safety Medical clinical staff, during work hours. Height will be measured in the standing position with a standard clinic stadiometer. Waist circumference will be assessed by using a tape measure snugly around each participant’s waist at the level of the iliac crests and measuring the circumference after expiration. Body weight will be measured with bare feet and in light clothes on a calibrated scale. Body fat will be estimated using a Bioelectrical Impedance Analyzer (Tanita). Blood pressures will be measured using an appropriately sized cuff with the subject in the seated position in a resting state.

The participants in the biomarkers nested study will be already participating in the Feeding America’s Bravest. The baseline collection time for the biomarkers coincide with the 1-year follow up. The second visit will be after 6 months of follow up or the original 18 months of follow up (see timeline in figure 1 and the second table below. Thus, the participants will be filling out the lifestyle/nutrition questionnaires/ anthropometrics and medical exam as explained previously in the protocol in each time point. The additional tests they will take are described below:

y,- Two EDTA blood collection tubes will be collected (<15ml of blood) in the fasting state (meaning no food or liquids except water for at least 12 hours before the appointment) at time point 12 and at 18 months of follow-up. Plasma and serum will be aliquoted, frozen at -80°C, stored and run in batches. Forty fatty acids will be analyzed including oleic, alphaE linolenic acid (w3), and alphaElinoleic (w6), which are reliable indicators of MUFA, tree nut and other healthy fat consumption. Analyses at time

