**4.4. List inclusion criteria**

IFD and Fishers members eligible for study consent and participation will include those: a)

permanently assigned to one of the 44 IFD stations or one of the 6 Fishers stations; b) with a fire department-provided medical exam in the last two years; c) at least 18 years of age; and d) full duty, modified or restricted duty status at the time of consent; OR e) Firefighters categorized as “Administrative Staff” by the IFD or Fishers will also be approached for participation and if they consent, be assigned to Group 1 because they are not assigned to specific fire houses.

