### **Follow-up Assessments:**

Every consented participant (regardless of intervention assignment) will be requested to complete the following every 6 months over 4 additional visits after the baseline assessment over the two years of the study:

The comprehensive nutritional-lifestyle questionnaire will be repeated (detailed above), as will the anthropometric measures (height, weight and body fat and resting blood pressure) will be collected in the same manner as described above for the baseline assessment.

Every 12 months, the Fire department provided, annual occupational medicine examinations (part of the firefighters’ usual care unrelated to the present study) will be provided by Public Safety Medical as per existing IFD/ Fishers policies. For consented participants ONLY, the medical exam results will be transferred to the Harvard Chan research team using the same established coded data transfer methods as described above for the baseline assessment of the same data points.

Consented participants will be assigned to Group 1 (Phase 1 nutritional intervention) or Group 2 (No intervention) according to their fire station’s cluster randomization.

For the nested biomarkers study the recruitment of participants will start in phase II following the below timeline:

Figure1. Current parent study timeline and biomarkers proposal timeline (in orange, the proposed study timeline)

[figure not shown]

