## PHASE II

### Mediterranean Diet Nutritional Intervention for 6 months for Groups 2 and 3 (and 4 in the final 6 months).

This intervention will be exactly as described above for Phase I, but will last 6 months. Afterwards, over the final 6 months of the study, the participants from Group 2 in Phase 1 will be encouraged to maintain eating Mediterranean style on their own using the support of the discount program, the study website and the support of fellow firefighters and family.

**Group 2: No intervention.** Over the next 12 months (year two). Phase 1 Group 1 participants will be encouraged to maintain eating Mediterranean style on their own using the support of the discount program, the study website and the support of fellow firefighters and family.

The table below summarizes data collection from all consented firefighter participants across the timeline of the 2-year study. Fishers Department FF will be joined to the study in the 12 months of follow up of the original Feeding America's Bravest

| Questionnaires/Measurements        | Baseline | 6months | 12months | 18months | 24 months |
|------------------------------------|----------|---------|----------|----------|-----------|
| Nutrition/Lifestyle questionnaires | X        | X       | X        | X        | X         |
| Blood Pressure                     | X        | X       | X        | X        | X         |
| Height/Weight                      | X        | X       | X        | X        | X         |
| Waist circumference                | X        | X       | X        | X        | X         |
| Body composition (Tanita)          | X        | X       | X        | X        | X         |
| Medical exam results transfer      | X        |         | X        |          | X         |

: .

The table below summarizes data collection from a random subset of consented firefighter participating in the biomarker study

| Biomarker proposal                                   | Time point1
(Dec2017/Jan 2018) | Time point2
(June2018) |
|------------------------------------------------------|-----------------------------------|---------------------------|
| Blood sample collection (fatty acids measurements)   | X                                 | X                         |
| Urine sample collection (hydroxytyrosol and tyrosol) | X                                 | X                         |

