| Total      | MDNI | Usual Care | SD       | Treated | Untreated | Difference | Alpha error | Power |

|      |     |     |     |      |      |      |      |     |
|------|-----|-----|-----|------|------|------|------|-----|
| 500  | 250 | 250 | 6.6 | 22.7 | 24.4 | -1.7 | 0.05 | 82% |
| 750  | 325 | 325 | 6.6 | 22.7 | 24.4 | -1.7 | 0.05 | 94% |
| 1000 | 500 | 500 | 6.6 | 22.7 | 24.4 | -1.7 | 0.05 | 98% |

The third example is for the prevalence of metabolic syndrome. We have found a metabolic syndrome prevalence of about 28% among career firefighters. Based on previous studies, we conservatively expect the MDNI to reverse at least 35% of cases.

| Population |      |            | Metabolic Syndrome Prevalence |         |           |            |             |       |
|------------|------|------------|-------------------------------|---------|-----------|------------|-------------|-------|
| Total      | MDNI | Usual Care | %
Δ                        | Treated | Untreated | Difference | Alpha error | Power |
| 500        | 250  | 250        | -35                           | 18%     | 28%       | -10.0%     | 0.05        | 76%   |
| 750        | 325  | 325        | -35                           | 18%     | 28%       | -10.0%     | 0.05        | 90%   |
| 1000       | 500  | 500        | -35                           | 18%     | 28%       | -10.0%     | 0.05        | 96%   |

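### Glucose, lipids and hs-CRP come only from fire department exams timed independently of the study, so the Phase 1 comparison of these outcomes need not be 12 months of MDNI against none

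*Protocol*

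**What the plan says.** **Baseline.** Section 4.6 (Baseline Assessment) states that "Public Safety Medical will transfer the results of the last existing fire department medical examination" to the research team. These results carry the "routine lab values (e.g. lipid panels, hs-CRP and glucose"). Section 4.4 admits members "with a fire department-provided medical exam in the last two years", and Section 4.5 excludes those "without a recorded fire department exam in the last two years". No new laboratory draw at entry is described for the parent trial.

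**Measured by the study itself.** Section 4.6 adds that "the baseline assessment will include anthropometric measures (height, weight and body fat estimates (Tanita) and resting blood pressure", with waist circumference in the same paragraph. These are repeated every six months. Laboratory values are not.

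**Follow-up.** Under Follow-up Assessments, the annual exams are described as usual care unconnected with the study and "will be provided by Public Safety Medical as per existing IFD/ Fishers policies". Section 4.7 repeats that they take place whether or not a member is in the study. In the data collection table under Phase II, the row "Medical exam results transfer" is marked at baseline, 12 and 24 months. No section gives a window around those times or says which exam counts as the month-12 value.

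**Use.** Section 5.1 compares Groups 1 and 2 over the first 12 months by intention to treat. Under Section 1, Group 2 then crosses over to the MDNI. Section 5.2 includes metabolic syndrome among its three power examples: prevalence is 28% without the intervention, and "we conservatively expect the MDNI to reverse at least 35% of cases".

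**The concern.** The table's labels suggest laboratory values at fixed study times, but the procedures tie them to a calendar that ignores study time. A follow-up exam early in Phase 1 reflects only a few months of MDNI in Group 1. One after month 12 may find Group 2 already on the MDNI. Both would tend to pull the between-group difference towards zero.

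The age of the baseline exam is a separate and lesser problem. It weakens baseline adjustment. It also stretches within-person change over time that precedes the intervention, and within-group change is where Section 5.1 expects its greatest power.

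The outcomes at stake are the laboratory part of the CVD risk profile in the Section 1 hypothesis and one of the three outcomes for which power is given. Later analysis rules can choose among dated exams, but they cannot supply a month-12 blood value that was never drawn.

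**Working it through.** **Step 1: timing.** Suppose exams are strictly annual and the baseline exam is *a* months old at the station's start, with 0 < *a* < 12.
- The next exam falls at month 12 − *a*, when Group 1 has had less than 12 months of MDNI.
- The one after falls at month 24 − *a*, which is after Group 2's cross-over.
- Example with *a* = 4: the exams fall at months 8 and 20. Neither compares 12 months with none.

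Only when *a* is near 0 or 12 does an exam fall close to month 12.

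**Step 2: longest within-person span.** The baseline exam can precede the start by 24 months and follow-up can come at month 12: 24 + 12 = 36 months, at most 12 of them intervention. This is an extreme. It needs someone with no exam in the 24 months before the start and none until month 12. With strictly annual exams the two are 12 months apart, of which 12 − *a* are intervention.

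**Step 3: reproduce the stated power (Section 5.2).** Inputs are 18% v 28%, two-sided 0.05 and equal arms. With p̄ the mean of the two proportions and *n* per arm:

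power = Φ{ [ |p1 − p2| − 1.96 √(2p̄(1 − p̄)/n) ] / √( [p1(1 − p1) + p2(1 − p2)]/n ) }

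For n = 250: (0.100 − 1.96 × 0.03764)/0.03737 = 0.70, and Φ = 75.9%.

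| Total | n per arm | Computed | Stated |
|---|---|---|---|
| 500 | 250 | 75.9% | 76% |
| 750 | 375 | 90.4% | 90% |
| 1,000 | 500 | 96.5% | 96% |

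The 750 row prints 325 per arm, which sums to 650 and gives 85.9%. The stated 90% corresponds to 375, which is used below. Like the protocol's own table, these figures ignore clustering by firehouse.

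**Step 4: illustrations.** These assume, without support in the protocol, that the 10-point effect builds evenly over 12 months.
- *Early exam, three quarters of the effect (9 months):* 28 − 7.5 = 20.5% v 28%. For n = 250: (0.075 − 1.96 × 0.03833)/0.03819 ≈ 0.00, and Φ = 50%.
- *Late exam, Group 2 one month into the MDNI:* 18% v 28 − 10/12 = 27.2%.
- *Late exam, Group 2 three months in:* 18% v 28 − 2.5 = 25.5%.

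| Scenario | 500 | 750 | 1,000 |
|---|---|---|---|
| Full contrast | 76% | 90% | 96% |
| Three quarters of effect | 50% | 67% | 79% |
| Control 1 month in | 69% | 85% | 94% |
| Control 3 months in | 53% | 70% | 82% |

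**Step 5: would a strict window repair it?** If exams are spread evenly over the year, months 9 to 12 hold 3/12 = 25% of them, or 125 per arm at 1,000. Mean exposure of 10.5 months gives 28 − 8.75 = 19.25% v 28%, with power 37%. Even the full 10 points gives only 47%. As the main rule, the window costs more than it recovers.

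**The case against.** **Choosing the exam is a matter for the analysis plan.** The protocol fixes a rule for baseline only. For follow-up it says every 12 months and marks a transfer at month 12; it prescribes neither the last exam before month 12 nor the first one after. That is correct, and the lack of a visit window is not held against it. What stands is that the protocol itself separates the date of the blood draw from study time.

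**An old baseline does not bias the comparison.** Randomised stations should have the same distribution of exam ages in expectation, and the Section 5.2 calculation uses no baseline. A reader might infer that the two-year allowance distorts the randomised contrast. The design does not support that inference.

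**The loss of power could be overstated.** With evenly spread exam dates and linear build-up, mean exposure would be 6 months and the contrast 23% v 28%, with power of 25%, 35% and 44%. A reader might take this as the expected result. The protocol gives no exam dates and no time course of effect, and Section 1 expects both the 6-month and the 12-month MDNI to improve risk profiles. Metabolic syndrome is undefined, and any part based on waist or blood pressure is measured by the study, so the whole 10 points need not shrink.

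**Usual-care exams are a deliberate, low-burden choice.** This also stands. The mixed and GEE models of Section 5.1 could use actual dates without discarding data, and the fix builds on that.

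**Conclusion.** The concern holds for glucose, lipids and hs-CRP, and for metabolic syndrome as far as it uses them. As written, the protocol does not secure a comparison of 12 months of MDNI with none for these outcomes, and mistimed exams in either direction would tend to shrink the difference. The baseline rule harms precision and within-group change, not the randomised contrast in expectation. mMDS, weight, body fat, waist and study-measured blood pressure are untouched, and so are the power examples for mMDS and body fat.

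The size cannot be determined from the protocol. The fall to 50%, 67% and 79% power is an illustration that assumes three quarters of the effect is present; it is not a forecast. The stated 76%, 90% and 96% are correct on their own inputs (with 375 per arm at 750), but they presuppose the full contrast for everyone. The point merits a change because the main remedy is to time an exam that is already provided.

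**What to change.** 1. **Schedule.** Where possible, place the existing annual exam near the month-12 study visit and before Group 2's cross-over. Public Safety Medical provides the exams and its staff take the study measurements, so no exam is added.
2. **Use dates.** Transfer the exam date with each result. In the planned mixed or GEE models, analyse laboratory outcomes by actual months since the station's start. Do not count any exam after Group 2's cross-over as Phase 1 control data. Include the age of the baseline exam as a covariate.
3. **Sensitivity analyses only.** Repeat the analysis with a narrow window around month 12, and with baseline exams restricted to the 12 months before the start. Neither should be the main rule: a months 9 to 12 window could drop about three quarters of participants if exams are spread evenly.

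The cost is some scheduling effort, a protocol wording change and slightly more analysis work.

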## 1. Specific Aims

1. Develop a multi-pronged, Mediterranean Diet Nutritional Intervention (MDNI) behavior change strategies including: diet/lifestyle education; discounted access to key Mediterranean diet foods; electronic education platforms and reminders. MDNI components will be refined via surveys, literature review and local/national firefighter input including labor/management and fire service focus groups.

Hypothesis (1). Cost-effective, fire-service MDNIs will be developed for the cluster-randomized, career firefighter diet intervention.

2. Cluster Randomized Diet Intervention-Phase I- the Indianapolis Fire Department (IFD) has over 1,000 members. All 44 IFD firehouses will be cluster randomized into two groups and then individual members will be consented regarding study participation. Group 1 will receive an active 12-month MDNI, while Group 2 will receive no intervention. Firefighters categorized as "Administrative Staff" by the IFD will also be approached for participation and if they consent, be assigned to Group 1 because they are not assigned to specific firehouses.

3. Cluster Randomized Diet Intervention -Phase II: Group 1 will cross-over to "self-sustained continuation" for 12 months to examine persistence of behavior change during this less intense, self-directed maintenance diet intervention. Group 2 will cross-over to receive the MDNI for 6 months (assessing a shorter MDNI), followed by a final 6 months of self-sustained continuation. An additional neighboring fire department, Fisher's (IN), will have its 6 firehouses randomized to receive the MDNI (Group 3) or no intervention (Group 4) for six months, and then individual members will be consented regarding study participation. After 6 months, the 3 stations in the MDNI (Group 3) will cross-over to "self-sustained continuation" for the last 6 months to examine persistence of behavior change during this less intense, self-directed maintenance diet intervention. Group 4 will cross-over to receive the MDNI for 6 months (assessing a shorter MDNI).

4. A similar 12-month Cluster Randomized Diet Intervention in the six fire stations of the Fishers (IN) Fire Department with a cross-over by the control group to intervention after 6 months will also be done.

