Our existing modified Mediterranean diet score (mMDS) will be further integrated with other validated scores and nutrition questionnaires. Questionnaires, mMDS and clinical data will be collected longitudinally throughout both phases of the Nutritional Intervention. The complete questionnaire has been entered into Qualtrics and is attached for the IRB's review.

Hypotheses (2-3). Both MDNI lengths will improve mMDS, reduce weight, and improve Cardiovascular Disease (CVD) risk profiles in career firefighters. The 12 month MDNI will produce greater persistence of adherence than a 6 month MDNI. Cost-effective methods that combine messaging and discounts for improving firefighters' diets will be developed and validated, and these low cost methods will be adaptable for widespread translation and implementation throughout the career fire service.

5. a. Conduct a nested evaluation of adherence biomarkers (urine tyrosol and hydroxytyrosol and plasma fatty acids) among randomly selected participants in the two Indianapolis MDNI arms (MD intervention vs. control, up to 100 in each).
- 5.b. Blood samples will also be stored for future analyses.
- 5.c. Stool samples will also be stored for microbiome analyses.

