Biomarkers and diet evaluation of food or nutrient intake are directly measured and can objectively estimate the consumption of specific dietary items without self-reporting biases and inaccuracies. Thus, by randomly assessing the adherence biomarkers within both the MD and control arms subsets of firefighters participating in the cluster-randomized controlled trial (Feeding America's Bravest), we can also better determine the validity of our dietary questionnaires with respect to Mediterranean diet-desirable fats. Blood samples can be used for further metabolomics analyses that will help us develop short-term indicators for assessing the effect of nutritional changes.

**In summary**, the negative effects of obesity and CVD on the fire service are recognized, but few effective preventive programs exist, and behavior change strategies must be improved. Evidence suggests that a Mediterranean diet nutrition intervention would be effective and well-received by career firefighters.

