**4.2. Indicate the study's duration - and the estimated date of study completion**

2 years. December 2018

**4.3. Indicate the total number of participants (if applicable, distinguish between the number of participants who are expected to be screened and enrolled, and the number of enrolled participants needed)**

1,000 career firefighters (500 assigned to group 1 and 500 assigned to group 2). We will approach as many eligible members as possible to consent at least 500 and up to 1,000 participants maximum. For the biomarkers nested study, a total of up to 100 firefighters, selected at random evenly from the existing study arms in Indianapolis

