## 5.2. Is there a sample size/power calculation?

☐ No ☒ Yes: If yes; describe the calculation and the scientific rationale, and, if applicable, by site and key characteristics such as participant demographics

Sensitivity analyses have been performed and demonstrate that even in the worst case scenario where only 500 firefighters would be enrolled, the study is well-powered for intention to treat comparisons of Mediterranean Diet Nutritional Intervention (MDNI) vs no intervention. Several conservative examples are given below for very small changes. However, consistent with previous studies, we expect the MDNI to actually produce larger changes that would be more easily measured. The first example assumes the MDNI can achieve a small increase in the mMDS of 6 points (about 1.0 times the population's baseline SD based on our cross-sectional study of mMDS)

For the biomarkers study spearman regression coefficients will be calculated to assess the association between 1) self-reported olive oil consumption, walnuts, tree nuts, other food groups of the Mediterranean Diet and the overall score on the modified Mediterranean Diet scale and the biomarkers. Linear regression models, adjusted for potential confounders will be fitted to study the association of previously mentioned foods and biomarkers. Changes in biomarkers and comparison between groups will be assessed using mixed modeling and generalized estimating equation models or other appropriate statistical tests depending upon the normality

| Population |      |            | Mmds |         |           |            |             |       |
|------------|------|------------|------|---------|-----------|------------|-------------|-------|
| Total      | MDNI | Usual Care | SD   | Treated | Untreated | Difference | Alpha error | Power |
| 500        | 250  | 250        | 5.6  | 27.3    | 21.3      | +6.0       | 0.05        | >99%  |
| 750        | 325  | 325        | 5.6  | 27.3    | 21.3      | +6.0       | 0.05        | >99%  |
| 1000       | 500  | 500        | 5.6  | 27.3    | 21.3      | +6.0       | 0.05        | >99%  |

The second example is for a small body fat change (1.7%) using typical values from our cross-sectional data

| Population |      |            | Body Fat |         |           |            |             |       |
|------------|------|------------|----------|---------|-----------|------------|-------------|-------|

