## 6. Recruitment Methods

### 6.1. Does the study involve the recruitment of participants?

☐ No: If no, skip to 7.1

☒ Yes: If yes; indicate how, when, where, and by whom participants will be recruited

**6. How:** Up to 1000 IFD members with permanent station assignments at one of the 44 Indianapolis fire houses will be recruited. The initial approach will be through a written announcement from the Chiefs of the Indianapolis Fire Department (IFD)/ Fishers FD and the firefighters' local union presidents (see attached letter) informing the IFD/ Fishers FD of the inauguration of the study and their opportunity to voluntarily participate. Next, human subjects-trained staff from Public Safety Medical (PSM) will visit each fire house to approach IFD/Fishers members for informed consent and determine their eligibility. Their recruitment script is attached. IFD/ Fishers members eligible for study consent and participation will include those: a) permanently assigned to one of the 44 IFD stations or one of 6 Fishers stations; b) with a fire department medical in the last two years; c) at least 18 years of age; and d) full, modified or restricted duty status at randomization; OR e) Firefighters categorized as "Administrative Staff" by the IFD/ Fishers will also be approached for participation. The fire department will notify PSM regarding criteria a, c, d and e and PSM has a record b (medical exams). First, they will provide a brief overview of the study to the firefighters by reiterating the information from the Chief and Union President's letter and the approved informed consent form. They will inform the fire house of its intervention assignment in the study – in other words, whether they will be receiving the nutritional intervention immediately (In Phase 1); or after 12 months (Phase 2). Next, each member will be offered an informed consent form to review on his/her own and will be allowed at least 15 minutes and longer if desired to review it on their own and to discuss it with their colleagues or others. Finally, each member will have a chance to ask the PSM staff questions individually in private areas of the fire house and may decide to sign the form or decline. IFD/Fishers members will be assured that participation status in the study is completely voluntary and will have no bearing on their employment with the department or on the occupational health care they receive from PSM. Consented participants will be assigned to the Phase 1 nutritional intervention (Group 1) or No intervention (Group 2) according to their fire station's cluster randomization. "Administrative" firefighters who consent will be assigned to Group 1 because they are not assigned to specific fire houses. For the biomarkers study randomly 100 participants (50 in each group) will be invited to participate in the study via email at the same time as the follow-up reminder. The recruitment will stop when we reach 60 participants (30 in each group)

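### The biomarker sub-study labels months 12 to 18 as MD versus control, but neither sampled arm is untreated in that window, so a between-arm comparison of change would take the wrong sign if the diet works

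*Protocol*

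**What the plan says.** **Timing.** The nested study takes blood and urine "at time point 12 and at 18 months of follow-up" (section 4.6, Baseline Assessment). The same section states: "The baseline collection time for the biomarkers coincide with the 1-year follow up". The data-collection table at the end of section 4.6 dates the two visits December 2017/January 2018 and June 2018 and also lists stool samples at both. Recruitment starts in Phase II (section 4.6, Follow-up Assessments) and is expected to take 4 to 8 weeks (section 6.1).

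**Contrast.** Aim 5a describes the sampled arms as "MD intervention vs. control, up to 100 in each". Section 2.1 gives the rationale in the same terms: "by randomly assessing the adherence biomarkers within both the MD and control arms subsets of firefighters". Only Indianapolis participants are sampled (Aim 5a and section 4.3).

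**Exposure.** In months 0 to 12 Group 1 has the active MDNI and Group 2 has none. For Phase II, Aim 3 says "Group 2 will cross-over to receive the MDNI for 6 months (assessing a shorter MDNI", while Group 1 moves to a self-sustained phase. In that phase Group 1 keeps the discount program, the study website and peer and family support (section 4.6, Phase II).

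**Analysis.** Section 5.2 plans correlations and adjusted linear regressions of reported intake against biomarkers. It then adds: "Changes in biomarkers and comparison between groups will be assessed using mixed modeling and generalized estimating equation models".

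**Size.** Aim 5a allows up to 100 in each arm. Section 4.3 gives "a total of up to 100 firefighters, selected at random evenly from the existing study arms". Section 6.1 invites 100 (50 per group) and adds: "The recruitment will stop when we reach 60 participants (30 in each group".

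**The concern.** The labels MD and control describe exposure correctly up to month 12. They do not describe months 12 to 18, the only interval over which a biomarker change can be measured. No sample is taken before the intervention, so the visit called baseline is, for Group 1, already a post-treatment measurement. If change from that visit is compared between arms under the Phase I labels, the treated-versus-untreated difference present at month 12 is subtracted out. What is left compares Group 2 starting the diet with Group 1 maintaining or losing it.

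This sub-study is the trial's objective check on adherence, meant to be free of self-report bias. Reported under the present labels, the change comparison could seem to contradict an intervention that worked. The precision intended is also unclear, because the protocol gives differing sizes and no detectable difference for the biomarkers.

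**Working it through.** The protocol gives no effect size, SD or power for the biomarkers, so there is no stated figure to reproduce. The check maps exposure to sampling times and works out what each contrast estimates.

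**Exposure at each sample (Aims 2 and 3; section 4.6)**

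| | Group 1 | Group 2 |
|---|---|---|
| Month 12 | after 12 months of active MDNI | untreated |
| Month 18 | 6 months into supported self-maintenance | after 6 months of active MDNI |

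The only group left untreated in months 12 to 18 is Group 4 in Fishers (Aim 3), which the biomarker study does not sample.

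**Contrasts.** Let E be the full 12-month MDNI effect on a biomarker, in the beneficial direction. Let r be the share of E that Group 1 still has at month 18, and s the share of E that Group 2 reaches after six months. Neither r nor s is in the protocol; both are assumptions. Expected values relative to no exposure are:

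- Group 1: E at month 12, rE at month 18
- Group 2: 0 at month 12, sE at month 18

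Therefore, Group 1 minus Group 2:

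- month-12 difference = E − 0 = E
- month-18 difference = rE − sE = (r − s)E
- difference in change = (rE − E) − (sE − 0) = (r − 1 − s)E

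| r | s | Month-18 difference | Difference in change |
|---|---|---|---|
| 1 | 0.5 | +0.5E | −0.5E |
| 1 | 1 | 0 | −1.0E |
| 0.75 | 1 | −0.25E | −1.25E |
| 0.5 | 0.5 | 0 | −1.0E |
| 0 | 1 | −1.0E | −2.0E |

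For any r between 0 and 1 and any s above 0, the difference in change is negative.

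Swapping the labels, so that Group 2 is the active arm and Group 1 the comparator, gives (1 + s − r)E. This equals the six-month effect sE only if r = 1; otherwise loss in Group 1 is added to uptake in Group 2.

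**Size.** A two-sample t-test at two-sided 0.05 and 80% power, treating people as independent, detects:

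| Per arm | Detectable difference |
|---|---|
| 100 (Aim 5a) | 0.40 SD |
| 50 (section 4.3) | 0.57 SD |
| 30 (section 6.1) | 0.74 SD |

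The normal approximation (1.96 + 0.84) × √(2/n) gives 0.72 SD at n = 30, which agrees closely. Because firehouses were randomized, the true values are larger by a factor that depends on how many participants share a house and how alike they are.

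**The case against.** A reader might infer that the protocol commits itself to the faulty analysis. It does not. The sentence in section 5.2 names changes and a group comparison. It does not specify a between-arm difference in change, and it does not say that the first sample will be a covariate. A mixed model with group, time and their interaction yields the month-12 difference, the month-18 difference and each arm's own change. The choice among these could properly sit in an analysis plan that is not shown. The word baseline can also be read simply as the first collection, since the same sentence places it at the one-year visit. All of this stands, and it limits the point to what the labels invite.

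A reader might also infer that the whole sub-study fails. It does not. The correlations and regressions of reported intake on biomarkers, which serve the questionnaire-validation purpose in section 2.1, need no control arm. The parent trial's Phase I comparison is not touched either.

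Nor is Group 1 simply off the intervention: it keeps several supports. That makes it less of an untreated comparator, not more.

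On size, it is tempting to say that three figures conflict. The 100s are ceilings and 60 lies under both, so the direct contradiction is between Aim 5a (per arm) and section 4.3 (in total).

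What the objection does not remove is that the protocol itself fixes the sampling times, the arms, the baseline label and the MD-versus-control label. It never says what the arms represent after the crossover.

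**Conclusion.** The concern holds for one use of the data: a between-arm comparison of month 12 to 18 change under the Phase I labels. That comparison has no untreated arm. It estimates (r − 1 − s)E, from −0.5E to −2.0E over the values tried. The negative sign requires only that the diet works, that Group 1 retains between none and all of its effect, and that Group 2 gains something in six months. The exact size depends on r and s. For example, a change contrast of −E together with a month-18 difference of zero requires both that Group 1 keeps the full effect and that Group 2 reaches it in six months, or another pair with r = s.

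The month-12 difference is the one treated-versus-untreated contrast available. It is sound only if three conditions are met:

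- **Timing.** Recruitment starts in Phase II and may last 4 to 8 weeks, so some first samples could follow the start of Group 2's MDNI.
- **Randomization.** Administrative staff are placed in Group 1 without randomization (Aim 2 and section 4.4), so including them would break the randomized comparison.
- **Clustering.** The analysis must allow for firehouse. The 0.74 SD at 30 per arm does not, and should not be printed as the study's detectable difference without that allowance.

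**What to change.** 1. State in Aim 5a and section 5.2 that the MD-versus-control biomarker contrast is the month-12 between-arm difference (12 months of MDNI against untreated). Analyse it as an outcome, not as a baseline covariate. Take time point 1 samples before Group 2's MDNI begins, leave non-randomized administrative staff out of this contrast, and account for firehouse clustering.
2. Analyse the month 12 to 18 change within each arm, as uptake in Group 2 and persistence in Group 1. Do not label it MD versus control. In section 4.6, call the month-12 sample time point 1 rather than baseline.
3. Give one biomarker sample size in Aim 5a, section 4.3 and section 6.1, with a detectable difference that allows for clustering. If 30 per arm stands, 0.74 SD is the figure before that allowance.

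**Cost.** The analysis and size changes are wording, using the same two visits and the same assays. Securing the first sample before Group 2 starts is a scheduling constraint on recruitment, and excluding administrative staff may slightly reduce the Group 1 participants available for the month-12 contrast.
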